#### 4.7 Microbiology/Virology

##### 4.7.1 Bacteriology of nasopharyngeal swabs

Swabs for microbiological analysis are stored in STGGB at -70 (in accordance with WHO guidelines). Presence of *Haemophilus influenzae*, *Moraxella catarrhalis* and *Streptococcus pneumoniae* will be identified using culture methods established in the Menzies laboratory. The antibiotic resistance phenotype will also be determined pre and post study medication administration.

Additionally, nucleic acids will be extracted from 0.2 ml of each nasopharyngeal swab specimen using the High Pure Viral Nucleic Acid kit (Roche Diagnostics, Australia), according to the manufacturer's instructions. Monospecific PCR and reverse transcriptase PCR (RT-PCR) method will be used to detect *Mycoplasma pneumoniae*, *Chlamydia pneumoniae* , coronaviruses , bocavirus  and human metapneumovirus (hMPV)  whereas multiplex PCR and RT-PCR will be used to detect adenovirus, parainfluenza (1, 2 3), influenza (A and B), and respiratory syncytial virus (RSV) . These methods have been previously validated in the QLD Paediatric Infectious Disease Laboratory.

##### 4.7.2 Respiratory pathogens in nasopharyngeal aspirates

NPA collected in the standard clinical manner will be frozen at -80°C. Upon thawing nucleic acids will be extracted from 0.2 ml of each NPA specimen using the High Pure Viral Nucleic Acid kit (Roche Diagnostics, Australia), according to the manufacturer's instructions. Monospecific PCR and reverse transcriptase PCR (RT-PCR) method will be used to detect *Mycoplasma pneumoniae*, *Chlamydia pneumoniae* , coronaviruses , bocavirus  and human metapneumovirus (hMPV)  whereas multiplex PCR and RT-PCR will be used to detect adenovirus, parainfluenza (1, 2 3), influenza (A and B), and respiratory syncytial virus (RSV) . These methods have been previously validated in the QLD Paediatric Infectious Disease Laboratory.

#### 4.8 Data analysis

**4.8.1 Primary outcome:** length of stay for bronchiolitis episode. The primary outcome (length of hospital stay) will be compared between infants receiving placebo or azithromycin using non-parametric analysis. Data within the Indigenous status will be analysed separately.

**4.8.2 Secondary outcome:** Length of time on supplemental oxygen; readmission to hospital within 6 months of this episode. All clinical secondary outcomes and laboratory data will also be analysed using non-parametric analysis. Categorical data will be compared using Chi square (or Fishers Exact).

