### **3.4 Background and rationale**

#### **3.4.1 Infants with bronchiolitis in the NT: burden and outcomes**

Bronchiolitis (with or without pneumonia) is the most common cause of admission in children aged under 12-months. In a Central Australian study, we described a prevalence of approximately 190 per 1000 children for RSV bronchiolitis. The prevalence of all causes of bronchiolitis would indeed be higher. In our setting, co-existent pneumonia is high in Indigenous children and, at the Royal Darwin Hospital (RDH), the majority of children with bronchiolitis are also treated with antibiotics. The co-existent pneumonia is likely related to the high carriage rate and early acquisition of respiratory pathogens in Indigenous children compared to non-Indigenous children. We have reviewed 100 charts of children hospitalised with bronchiolitis at the RDH and found that the readmission rate of Indigenous children for their next bronchiolitis episode within 6-months was 30% (unpublished). As the majority of these children hospitalised for bronchiolitis are retrieved from remote communities, the impact of the illness and costs plus social dislocation is significant. Furthermore recurrent lower respiratory tract infection is an independent significant risk factor for the later development of bronchiectasis and lower pulmonary function in later years. In addition the severity of the hospitalised episode (oxygen requirement and length of hospital stay) were also risk factors for development of bronchiectasis. In our retrospective chart review we found that Indigenous infants hospitalised with bronchiolitis had more severe bronchiolitis than non-Indigenous infants (unpublished). In Indigenous infants, the severity score at presentation, number of days requiring oxygen and length of hospitalisation were all significantly worse or longer than in non-Indigenous infants ( $p=0.0001$ ,  $0.004$ ,  $0.001$  respectively). Thus any intervention that is efficacious in reducing the

severity of bronchiolitis and/or readmission for bronchiolitis in Indigenous children would be beneficial in both short and long term outcomes.

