#### 4.2.1 Enrolment procedure

1. After obtaining informed consent, complete a consent form and give a copy of this and the information sheet to the carer.
2. Complete the enrolment form and the as much of the demographic and medical history as possible from the carer.
3. Use the date of birth and Indigenous status data to determine the treatment strata. There are 4 possible strata
  - Strata 1** Indigenous 6 months and less
  - Strata 2** Non Indigenous 6 months and less
  - Strata 3** Indigenous older than 6 months
  - Strata 4** Non Indigenous older than 6 months
4. Complete a chart notification sticker and stick in the child's medical chart

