#### 4.2.2 Randomisation and blinding of treatment allocation

This is a double-blind, randomised, placebo-controlled trial with concealed allocation. The study medications will be assigned the labels A, B, C or D (two labels assigned to placebo azithromycin and two assigned to azithromycin) by an independent person of the study at Menzies School of Health Research. Neither the study team (researchers, hospital staff) nor parents will know which treatment group (placebo or azithromycin) the infant has been assigned until the results have been analysed. Placebo azithromycin has been specifically manufactured by IDT Australia Limited (Melbourne, Victoria) and has a similar smell and taste to active azithromycin. The manufacture of placebo was

primarily for our NHMRC funded international study on bronchiectasis in Indigenous children.

The treatment allocation list has been computer generated by using stratified block randomisation. There are 4 sheets, each corresponding to the treatment strata. Treatment allocation has been concealed by black sticker. Upon enrolment an infant will be assigned to the next treatment on the appropriate stratified list and the treatment (A, B, C or D) revealed.

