#### **4.3 Study size**

We plan to enrol 100 infants total. Children will be stratified by age (6 months and less and over 6 months), Indigenous status (Indigenous and non Indigenous) and site (Darwin and Townsville). The mean length of stay for bronchiolitis at Royal Darwin Hospital is 96 hours. To detect a mean difference of 24 hours in length of stay between treatment groups with an alpha of 0.05 and a power of 90%, the required sample size is 23 infants per group.

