#### 4.6 Clinical assessment

Children enrolled in this study will be managed by hospital staff according to standard clinical practice for the management of bronchiolitis. They are not exempt from receiving any care or management protocol specified by the attending physician.

A standardised sheet will be used to collect clinical data. Demographic information and medical history will be obtained from the primary care-giver and from hospital records. The primary and secondary outcome measures (described below) will be monitored from the medical chart until the acute study end-point has been reached (defined as >16 hours off supplemental oxygen and infant is feeding well). Clinical assessment data includes oxygen requirement and level, physiological measurements for clinical severity score (respiratory rate, accessory muscle use, degree of wheeze), other physiological measurement (temperature, heart rate), requirement for other therapies (IV fluids, nutrition, antibiotics). In addition routine investigatory parameters (FBC and chest x-ray findings) will be recorded.

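### The overall test of length of stay does not carry the randomisation strata, although the protocol itself shows Indigenous status to be prognostic; the cost is slight conservatism and at most a few points of power

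*Protocol*

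**What the plan says.** - Protocol 4.2.2: "The treatment allocation list has been computer generated by using stratified block randomisation".
- Protocol 4.2.1: "There are 4 possible strata", formed by crossing age (up to 6 months, or older) with Indigenous status. Section 4.2.2 gives one allocation sheet per stratum.
- Protocol 4.3 adds a third factor: "Children will be stratified by age (6 months and less and over 6 months), Indigenous status (Indigenous and non Indigenous) and site (Darwin and Townsville". That would be eight cells if fully crossed, which does not match the four sheets.
- Protocol 3.4.1 gives the result of the sponsor's chart review for Indigenous infants: "number of days requiring oxygen and length of hospitalisation were all significantly worse or longer than in non-Indigenous infants". The list there opens with severity on arrival. The p-values for the three measures are 0.0001, 0.004 and 0.001, the last being for length of stay.
- Protocol 4.8.1 sets the primary comparison: "The primary outcome (length of hospital stay) will be compared between infants receiving placebo or azithromycin using non-parametric analysis". It then adds: "Data within the Indigenous status will be analysed separately". No rule is given for combining the separate results.
- Protocol 4.8.2 applies the same type of analysis to time on oxygen.

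**The concern.** Stratified blocks balance the arms on the strata. If a stratum predicts the outcome, the treatment difference then varies less from trial to trial than a plain two-group test assumes, because that test still counts the between-stratum spread as noise. The test therefore rejects less often than its nominal level when there is no effect, and gives up some power when there is one. The protocol balances on Indigenous status, reports that it is associated with longer stay, and then describes an overall comparison that does not use it. The separate analyses by Indigenous status do not recover the loss. Each uses only part of the 100 infants, and they are not pooled into one stratified test. At stake is some power for the primary outcome and for oxygen time. False-positive control is not at risk.

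**Working it through.** **Inputs from the protocol.** 100 infants, 24 h difference, alpha 0.05, power 90%, 23 per group (4.3); p=0.001 for Indigenous status and stay, and a review of 100 charts (3.4.1); equal allocation, inferred from two labels per treatment (4.2.2).

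**Assumptions.** Two-sided test; the p-value comes from the 100 charts; 60% Indigenous and blocks of 4 in the simulations; normal outcome. A rank test is unchanged by a monotone transformation, so the normal model also stands for skewed stay if the effect is additive on a transformed scale such as the log.

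**1. The plan's own figure.** The SD is not stated, so 23 per group cannot be reproduced directly. Solving n = 2(1.960 + 1.282)²·SD²/24² for n = 23 gives SD = 25.1 h. With SD 25 h, n = 2 × 10.51 × 625/576 = 22.8, rounded up to 23. The implied standardised effect is 24/25 = 0.96 SD. If the SD were 48 h, it would be 24/48 = 0.5 SD.

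**2. How prognostic is Indigenous status?** p = 0.001 gives z = 3.29. With a fraction f Indigenous among 100 charts, the gap is 3.29/√(100 f(1−f)): 0.66 SD at f = 0.5, 0.72 at 0.7 and 0.82 at 0.8. Share of variance: R² = 3.29²/(3.29² + 98) = 0.10.

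**3. True size of an unstratified test.** Size = 2[1 − Φ(1.96/√(1−R²))]. At R² = 0.10 this is 2[1 − Φ(2.066)] = 0.039. Simulated rank tests gave 0.037 to 0.040 (2,500 runs per setting). A separate simulation with a 0.72 SD gap gave about 0.043. At R² = 0 the size is 0.05.

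**4. Power, analytic, R² = 0.10.** With SE = SD·√(2/n), the unstratified power is Φ[(24/SE − 1.96)/√(1−R²)] and the stratified power is Φ[24/(SE·√(1−R²)) − 1.96].

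| Per group | SD (h) | Unstratified | Stratified |
|---|---|---|---|
| 23 | 25 | 91.4% | 92.9% |
| 50 | 25 | 99.9% | 99.9% |
| 50 | 36 | 92.6% | 94.0% |
| 50 | 48 | 71.5% | 75.0% |

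**5. Power of the rank tests, simulated, 100 infants, 0.72 SD gap.** At an assumed 0.5 SD effect, power is 64% unstratified, 67.5% with van Elteren stratified by Indigenous status, and 66% over the four lists. At 0.96 SD it is 99.5% against 99.7%.

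**6. What stratifying can cost.**
- Strata not prognostic (R² = 0), four lists: 88.4% against 89.2% unstratified at 50 per group with SD 36 h, and 83.2% against 85.6% at 23 per group with SD 25 h. These are losses of 0.8 and 2.4 points.
- Eight cells in the test, 0.72 SD gap: 63% against 64% at 100 infants and 0.5 SD, and 79% against 84% at 23 per group. Crossing in site spends the gain, and more in a small trial.

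**The case against.** The strongest reply is that 4.8.1 names no test. A van Elteren test is also non-parametric, the sentence that follows does use Indigenous status, and a statistical analysis plan not shown may settle the matter. This stands in part. That the overall test is unstratified is the natural reading of a comparison described only as placebo against azithromycin, but the protocol does not say so outright. The separate analyses are no answer, since nothing pools them.

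A reader might infer several stronger things that the documents do not support:

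- *That the analysis uses no stratification factor.* The sentence on separate analyses by Indigenous status shows otherwise.
- *That all the stratification factors are known to predict stay.* Section 3.4.1 supports this for Indigenous status only. Nothing is said about age or site.
- *That much power is lost.* Losses of 8 to 16 points need stratum gaps of 1.0 to 1.3 SD together with a 0.5 SD effect. Those gaps exceed the 0.66 to 0.82 SD that p=0.001 implies.
- *That stratifying costs nothing.* Step 6 of the working shows otherwise.
- *That omitting the baseline severity score is an error.* Section 4.6 collects "physiological measurements for clinical severity score (respiratory rate, accessory muscle use, degree of wheeze", but the score is not a stratification factor, and adjusting for it is optional.

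**Conclusion.** The point holds as a modest improvement to the analysis. The protocol randomises within strata that include a factor it reports as prognostic, and then describes an overall comparison without them. On the protocol's own p-value, the unstratified rank test runs at about 4% instead of 5%. At 100 infants the loss is about 2 to 4 power points if the true effect is near 0.5 SD, and almost none if the SD is about 25 h. Which case applies cannot be told from the protocol, because it gives no SD. The size of the point rests on the p-value coming from the 100 charts and on the trial having a similar gap between Indigenous and non-Indigenous infants. A reader might take the mismatch as a threat to validity. It is not: the error is conservative and does not raise the false-positive rate.

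**What to change.** 1. Reconcile the four strata of 4.2.1 and 4.2.2 with 4.3, which also lists "Indigenous status (Indigenous and non Indigenous) and site (Darwin and Townsville", so that the strata used for allocation are clear.
2. In 4.8, make the overall comparison of length of stay, and likewise of time on oxygen, a van Elteren (stratified Wilcoxon) test. Stratify by Indigenous status or by the four age-by-Indigenous lists actually used. Do not cross all eight cells in the test.
3. Report a matching stratified Hodges-Lehmann difference in hours with its 95% CI.
4. Keep the separate analyses by Indigenous status, labelled as subgroup results.
5. Optionally, add a supporting analysis adjusted for baseline severity score.

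The cost is a sentence or two in 4.8. The stratum variables are already needed to randomise each infant. The downside is a loss of about 1 to 2 power points over the four lists if the strata turn out not to be prognostic. Stratifying by Indigenous status alone makes that loss smaller.

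### The primary comparison names no baseline severity covariate although severity data are collected: a cheap gain in precision is left unused, but the planned test is valid

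*Protocol*

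**What the plan says.** - **Analysis.** Protocol 4.8.1 states that length of stay "will be compared between infants receiving placebo or azithromycin using non-parametric analysis", and that the data are also analysed separately by Indigenous status. Section 4.8.2 applies non-parametric analysis to time on supplemental oxygen. Neither section names a specific test or a baseline covariate.
- **Data.** Section 4.6 lists oxygen requirement and level and "physiological measurements for clinical severity score (respiratory rate, accessory muscle use, degree of wheeze") among the items on the standardised sheet. It does not name a pre-dose time point.
- **Randomisation.** Section 4.2.1 defines four strata from age and Indigenous status; section 4.3 adds site. Severity is not a stratum in either section.
- **Background.** The chart review in 3.4.1 reports that in Indigenous infants, compared with non-Indigenous infants, "the severity score at presentation, number of days requiring oxygen and length of hospitalisation were all significantly worse or longer".
- **Sample size.** Section 4.3 plans 100 infants. Its calculation starts from a 96 h average stay at the Darwin site and a target difference of 24 h, and concludes: "alpha of 0.05 and a power of 90%, the required sample size is 23 infants per group". No SD is stated.

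**The concern.** How sick an infant is at entry plausibly predicts how long the infant stays. The acute end-point in 4.6 includes a period off oxygen, so oxygen need at entry should bear on time to recovery. If so, a comparison without severity leaves explainable variation in the error term. Stratified randomisation does not recover it, because infants in the same age and Indigenous-status stratum can still differ in severity.

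What is at stake is precision for length of stay and time on oxygen. It matters most in the separate analyses by Indigenous status. These carry much of the trial's rationale (3.4.1 and 3.4.2) and necessarily have fewer infants per arm than the whole trial.

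**Working it through.** **Inputs from the protocol (4.3).** Difference 24 h; alpha 0.05 (taken as two-sided, since sidedness is not stated); power 90%; 23 per group; planned total 100. Section 4.2.2 assigns two of four labels to each treatment, which implies 1:1, so 100/2 = 50 per group.

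**Assumptions (not in the protocol).** Severity–stay correlation rho = 0.5, range 0.3 to 0.6; alternative SDs of 36 h and 48 h; 25 per arm in an Indigenous-status analysis (an equal split of 50 per arm).

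**Step 1: the SD behind 23 per group.** The figure cannot be checked forwards because no SD is given. Solved backwards for a two-sample t-test, 23 per group at 90% power needs a standardised difference d = 0.977, so SD = 24/0.977 = 24.6 h. The normal approximation gives 24 × sqrt(23/2)/(1.960 + 1.282) = 25.1 h.

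**Step 2: effect of adjustment on the SD.** Residual SD = SD × sqrt(1 − rho²).
- rho 0.3: sqrt(0.91) = 0.954, a fall of about 5%
- rho 0.5: sqrt(0.75) = 0.866, a fall of about 13%
- rho 0.6: sqrt(0.64) = 0.800, a fall of 20%

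**Step 3: power for a 24 h difference (t-test approximation).**

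| SD | n per arm | unadjusted | rho 0.3 | rho 0.5 | rho 0.6 |
|---|---|---|---|---|---|
| 24.6 h | 23 | 90.0% | 92.5% | 96.3% | 98.2% |
| 24.6 h | 25 | 92.3% | 94.4% | 97.4% | 98.9% |
| 24.6 h | 50 | 99.8% | 99.9% | >99.9% | >99.9% |
| 36 h | 50 | 91.0% | 93.3% | 96.8% | 98.5% |
| 48 h | 25 | 41.0% | 44.3% | 51.6% | 58.1% |
| 48 h | 50 | 69.7% | 73.7% | 81.6% | 87.2% |

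**Step 4: check with rank tests.** The plan is non-parametric, so the t-test figures are only a guide. Length of stay was simulated as log-normal, mean 96 h against 72 h, comparing Mann-Whitney with rank analysis of covariance (4000 runs per case).
- SD 24.6 h, 23 per arm, rho 0.5: 96.1% to 98.7%, a gain of 2.6 points (the t-test gain is 6.3).
- SD 48 h, 50 per arm, rho 0.5: 83.8% to 92.1%; an independent repeat gave 84.6% to 91.6%. The gain is 7 to 8 points (the t-test gain is 11.9).
- SD 48 h, 50 per arm, rho 0.3: 84.0% to 86.5%.
- SD 48 h, 23 per arm, rho 0.5: 48.7% to 60.3%.
- SD 25 h, 50 per arm: both tests at about 100%.

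The SD in these runs is that of the placebo arm. The effect is proportional, so the treated arm's SD is 72/96 = 0.75 of it. This is one reason why the simulated powers are not directly comparable with the table.

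**Step 5: validity.** With no treatment effect (SD 48 h, 50 per arm, rho 0.5), rejection rates were 5.0% for Mann-Whitney and 4.9% for the adjusted test.

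**Step 6: chance imbalance.** A one-standard-error imbalance in severity moves the estimated difference by rho × sqrt(2/n) × SD. At rho 0.5 and SD 24.6 h this is 0.5 × 0.295 × 24.6 = 3.6 h (23 per arm) or 0.5 × 0.200 × 24.6 = 2.5 h (50 per arm). The standard error of the difference itself is 0.295 × 24.6 = 7.3 h or 0.200 × 24.6 = 4.9 h, so each shift is half a standard error and already lies within the variation that the unadjusted test allows for.

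**The case against.** The case against acting is substantial, and most of it stands.

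- **Little power is lost on the protocol's own figures.** The trial plans 100 infants, not 46. At the implied SD, power is 99.8% without adjustment, and an analysis with 25 per arm would still have 92.3%. This stands. A reader might take the 6.3-point gain at 23 per group as the cost to this trial, but that is not the planned enrolment, and the rank tests gain only 2.6 points there.
- **The larger gains rest on assumptions.** No SD of 36 h or 48 h and no correlation appears in the protocol. This also stands, with the qualification that the 24.6 h is itself only back-solved.
- **The chart review does not show that severity predicts stay within strata.** A reader might infer that from 3.4.1, but it reports a contrast between Indigenous and non-Indigenous infants, and Indigenous status is already a stratum and analysed separately. Eligibility (4.1) also narrows the severity range by requiring oxygen need and excluding infants on oxygen for more than 24 hours, which may lower the correlation.
- **A pre-dose value is not guaranteed.** Section 4.6 names no time point. Every eligible infant needs oxygen, so some pre-dose oxygen record is likely, but completeness is unknown.
- **Covariates are often left to the SAP.** No SAP is at hand, and the term non-parametric does not exclude a rank-based adjusted method. This limits the point to an improvement: section 4.8 as written describes a comparison between arms with no covariate, and does not commit to adjustment.

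**Conclusion.** The point holds as one of efficiency only. Section 4.8 names no baseline covariate, severity data are collected, and randomisation does not stratify on severity.

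A reader might go further and conclude that the comparison is biased or invalid because severity is left uncontrolled. The documents do not support that: randomisation balances severity on average, chance imbalance is covered by the test's error rate, and the simulated type I error is about 5%.

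The gain in power is negligible for the whole trial at the implied SD of 24.6 h and 50 per group, although the residual SD would still fall by about 5% to 20% at an assumed correlation of 0.3 to 0.6. The gain becomes material in the separate Indigenous-status analyses, chiefly if the SD is well above 24.6 h, or for the whole trial if the SD is nearer 48 h. All of these sizes depend on an SD and a correlation that the protocol does not give. This is a cheap improvement, not the correction of an error.

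**What to change.** Before unblinding, pre-specify in section 4.8:
- rank analysis of covariance as the comparison for length of stay and for time on supplemental oxygen;
- as covariate, the last clinical severity score charted before the study dose, or the pre-dose oxygen level if the score is incomplete. Later values may be affected by treatment and must not be used;
- a simple rule for infants with no pre-dose value, such as a missing-value indicator;
- the unadjusted non-parametric test as a sensitivity analysis.

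If an SAP already specifies such an adjustment, it is enough to confirm that and align 4.8 with it.

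The cost is one or two sentences and no extra infants or visits. No new data collection is needed, provided that the chart review confirms pre-dose values are recorded. The small downsides are the missing-score rule and an adjusted rank result that is slightly harder to explain than a plain two-group test.

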#### **4.2.3 Clinical samples**

##### **4.2.3.1 Nasopharyngeal swabs**

- a) One nasopharyngeal swab is obtained prior to the administration of the study medication. A second nasopharyngeal swab is obtained 48 hours post administration of study medication. The swabs are stored in separate vials of STGGB medium and stored at -70 degrees prior to dispatch to the Menzies laboratory for processing.

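### The only categorical test named in 4.8.2 (chi-square or Fisher's exact) makes no use of the pre-dose swab: valid between arms at 48 hours but possibly inefficient, and unsuited to any pre/post comparison

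*Protocol*

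**What the plan says.** Section 4.2.3.1 sets two swabs per infant: "One nasopharyngeal swab is obtained prior to the administration of the study medication", and "A second nasopharyngeal swab is obtained 48 hours post administration of study medication". Section 4.7.1 says that the presence of three bacterial species "will be identified using culture methods established in the Menzies laboratory", and adds: "The antibiotic resistance phenotype will also be determined pre and post study medication administration".

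Section 4.8.2 gives the analysis in two sentences. The general one is "All clinical secondary outcomes and laboratory data will also be analysed using non-parametric analysis". The specific one is "Categorical data will be compared using Chi square (or Fishers Exact"). No paired, stratified or baseline-adjusted test is named. The section does not say which carriage or resistance comparison the categorical rule serves: arms at 48 hours, or before against after.

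The named secondary outcomes are "Length of time on supplemental oxygen; readmission to hospital within 6 months of this episode". Carriage and resistance are not among them, and the sample size in 4.3 does not rest on them.

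**The concern.** Two yes/no results from one infant 48 hours apart are likely to be correlated. Chi-square and Fisher's exact assume independent observations and have no place for a baseline value. The rule can be applied to the swabs in two ways:

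- **Between arms at 48 hours.** The test is valid, but it leaves out a pre-dose result that may predict the 48-hour result well. Chance imbalance in pre-dose carriage then adds noise to the difference between arms.
- **Before against after, within an arm.** The independence assumption fails. With positive correlation the test rejects too rarely and loses power.

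The rationale for azithromycin (3.4.2) leans on bacterial colonisation, and the paired swabs are the planned direct look at an antibacterial effect. Precision in that comparison could be given up although the data to recover it are already being collected.

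**Working it through.** **Inputs from the protocol.** 100 infants in total (4.3). Two of four labels go to each treatment (4.2.2), which implies 1:1 allocation, so 100/2 = 50 per arm. One swab before dosing and one at 48 hours (4.2.3.1).

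**Inputs that are assumptions.** The protocol gives no carriage rate, persistence, new-detection rate or pre/post correlation. All infants are taken to have both swabs, and tests are two-sided at 5%. There is no stated power figure for carriage to reproduce.

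**Tests compared by simulation.** Between arms: chi-square on the 48-hour swab alone, against Mantel-Haenszel stratified by the pre-dose result. Within an arm: unpaired chi-square on before and after, against McNemar, (b - c)²/(b + c), where b and c count infants who lose or gain the organism.

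**1. Between arms, correlation set directly.** Carriage before dosing and on placebo is p, falling on azithromycin as shown. Each cell is power by chi-square, then stratified.

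| Carriage | phi 0 | phi 0.2 | phi 0.3 | phi 0.5 |
|---|---|---|---|---|
| 50% to 25% | 0.747, 0.742 | 0.750, 0.763 | 0.746, 0.780 | 0.748, 0.857 |
| 60% to 35% | 0.734, 0.717 | 0.733, 0.726 | 0.731, 0.746 | 0.734, 0.833 |
| 40% to 20% | 0.593, 0.586 | 0.596, 0.607 | 0.595, 0.629 | 0.597, 0.714 |
| 70% to 45% | 0.737, 0.726 | 0.742, 0.740 | 0.742, 0.762 | 0.734, 0.838 |

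At phi 0 to 0.3 the change runs from -1.7 points (0.717 - 0.734) to +3.4 points (0.629 - 0.595). At phi 0.5 it is +10 to +12 points.

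**2. Between arms, persistence set directly.** With pre-dose carriage p0, persistence s and new detection g, 48-hour carriage is p1 = p0·s + (1 - p0)·g, and phi = (s - g)·√[p0(1 - p0) / (p1(1 - p1))]. Take p0 = 60% and g = 10%:

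- Placebo, s = 85%: p1 = 0.51 + 0.04 = 0.55; phi = 0.75·√(0.24/0.2475) = 0.74.
- Azithromycin, s = 50%: p1 = 0.30 + 0.04 = 0.34; phi = 0.40·√(0.24/0.2244) = 0.41.

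| p0 | s placebo | s azithromycin | g | Chi-square | Stratified |
|---|---|---|---|---|---|
| 60% | 85% | 50% | 10% | 58% | 74% |
| 60% | 85% | 60% | 10% | 34% | 48% |
| 40% | 85% | 50% | 10% | 32% | 46% |
| 80% | 85% | 50% | 10% | 83% | 91% |
| 60% | 70% | 40% | 30% | 46% | 46% |

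The first three rows gain about 14 to 16 points. The fourth gains about 8, because power is already high and phi on azithromycin is only 0.32. In the last row phi is 0.39 on placebo and 0.10 on azithromycin, and the gain vanishes.

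**3. Size of the between-arm tests.** With no treatment effect, the 48-hour chi-square rejects about 5.5% to 5.8% of the time and the stratified test about 5%. Both are acceptable.

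**4. Chance imbalance.** At 60% carriage the SD of the pre-dose difference between arms is √(2·0.6·0.4/50) = 0.098. The part carried to 48 hours is 0.75·0.098 = 0.073 if both arms follow the placebo slope (0.85 - 0.10). It is √[(0.24/50)(0.75² + 0.40²)] = 0.059 if the azithromycin arm follows its own slope (0.50 - 0.10). The ordinary standard error already contains this, so it is lost precision and not bias.

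**5. Within an arm.** With carriage steady at 50%, the unpaired chi-square rejects 3.2%, 2.4% and 0.7% of the time at phi 0.2, 0.3 and 0.5, against a nominal 5%. Power at p0 = 60%, g = 10%:

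- s = 65%: unpaired 38%, McNemar 70% to 71%.
- s = 50%: unpaired 83%, McNemar 94%.

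Across the carriage settings in step 1, the loss against McNemar is about 5 to 8 points at phi 0.2 and 14 to 26 points at phi 0.5.

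**The case against.** The strongest case on the other side is that the protocol states no error here. A reader might infer that the two swabs will be tested as if they came from separate infants, but 4.8.2 nowhere says so. The categorical rule can be read as a comparison of arms, and that comparison is valid at 48 hours. The general sentence on laboratory data allows non-parametric methods, and McNemar's test is one. Carriage and resistance are unlisted laboratory measures, and an analysis plan not shown here could specify their analysis. The gain from stratifying also depends on a correlation that nobody has stated.

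Much of this stands. A reader might also call the pre-dose swab wasted. It is not: it describes baseline and can inform the co-infection question in 3.1(b) and 3.2(c). Nor is it right that an unpaired pre/post test would almost never find a real change, since its power is 38% to 83% in the settings above. Resistance is not a paired value on every infant, because it exists only where an organism grows.

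What does not stand is that the matter was simply left open. The specific sentence for categorical data names two tests, and neither uses the pairing that the design provides.

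**Conclusion.** The point holds as one of efficiency and clarity. The named categorical tests do not use the pre-dose swab and would not suit a pre/post comparison. With 50 per arm, stratifying changes between-arm power by about -2 to +4 points at phi 0 to 0.3. It adds about 10 to 16 points in most of the strong-correlation settings tried, and about 8 where carriage is 80% and the azithromycin-arm correlation is weak. All these figures rest on assumed rates and on complete pairs of swabs. Strong correlation over 48 hours in the same child is plausible, but the protocol gives no data on it.

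The documents do not support a claim that the 48-hour chi-square is invalid or biased. They also do not support any consequence for length of stay, oxygen time or readmission. The clinical hypothesis in 3.1(a) is tested by those outcomes and not by carriage.

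**What to change.** In 4.8.2, add a rule for swab results:

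- Compare 48-hour carriage of each organism between arms by a Mantel-Haenszel test (exact if sparse), or by logistic regression, stratified by the same infant's pre-dose carriage. Report a risk difference with 95% CI.
- Use McNemar's test for any within-arm pre/post change.
- Analyse resistance as carriage of a resistant isolate (yes/no) among all swabbed infants, so that the pre-dose stratum is defined for everyone.
- Keep chi-square or Fisher's exact for outcomes measured once, such as readmission.

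The cost is a few lines of text. Both swabs are already planned, so no new data are needed. The downsides are sparse strata for rare organisms, which the exact test handles, and no gain or a loss of up to about 2 points of power if the pre/post correlation is weak.
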